The difficulties encountered with PTx have to some extent been compensated by a very selective attitude towards the donors, but thereby making pancreas grafts a scarce resource. In contrast to other abdominal transplantations such as liver transplantation (LTx) and kidney transplantation (KTx), where repeated biopsies have been used for immunosurveillance, percutaneous biopsies of the pancreas-graft have traditionally been avoided due to a high rate of biopsy-related complications (exocrine leaks/fistulas and bleeding episodes). Thus, fear of acute rejections and lack of adequate rejection markers, have led to a rather intensive immunosuppressive load in PTx recipients.

Solitary pancreas transplantation (SPT) has traditionally been subjected to even higher complication and rejection rates, with inferior graft and patient survival - thus favoring the combined SPK procedure. This has been attributed to an even worse rejection monitoring capability, without a”reporter”/sentinel allograft kidney. No biochemical markers have proven to be effective in rejection surveillance.

Pancreas graft thrombosis is a feared complication in the postoperative course, partly due to the oversized vessels used (coeliac trunk/superior mesenteric artery/portal vein) in conjunction with the low blood flow through an isolated pancreas graft. In the native setting, these vessels also serve the intestines and spleen. Therefore, PTx poses a delicate balance between thrombosis and bleeding complications.

*End stage type 1 diabetes is a devastating chronic disease. PTx offer long term insulin-independency. Efforts should be made to define robust patient selection criteria and offer eligible patients insulin-independency before severe diabetic complications appear.*

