**1.1 The Norwegian experience**

PTx is performed at one single national center in Oslo, and from 1983 to date 300 procedures have been performed (7-11). In recent years, the activity has increased; 22 were performed in 2011 and 28 in 2012. Approximately 9 out 10 PTx’s have been SPK’s, hence only about 10% have been SPTs. In the first period from 1983 through 1987, a duct-occluded segmental pancreas was used for transplantation. From 1988, the whole pancreas graft was used, and the exocrine secretion was drained by anastomosing the duodenal segment to the urinary bladder. This technical solution was chosen partly because it offered some sort of rejection monitoring, by urine amylase counts and cystoscopic pancreas biopsies. However, many patients suffered from chemical cystitis and metabolic acidosis, due to loss of bicarbonate. In 1998 the urinary bladder anastomosis was abandoned, in favor of the more physiological enteric anastomosis, the duodenal segment being connected to the proximal jejunum. However, this solution offered even less options to monitor upcoming rejections, as percutaneous biopsies was mostly avoided due to the previously mentioned hazards.

We have recently examined (12) all PTx’s performed at our hospital during 2006-2010 (n=61; 59 SPK, 2 PTA). Our overall surgical complication rate has decreased from earlier years, but we still suffer a substantial rate of reoperations (about 30% of patients), mainly caused by exocrine leakage, bleeding and vein thrombosis. When comparing the populations with or without reoperation, higher donor age had a significant negative impact. No significant effect of donor age on graft survival was observed. There was a tendency towards better results in female recipients, both regarding surgical complications and graft survival. The rejection rate (altogether about 30%) was significantly higher in the graft loss group, and reoperations were insignificantly associated with graft loss.

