**2.1** **Primary objectives**

- Compare the incidence of *acute rejection episodes* at 6, 12, 36 and 60 months after pancreas transplantation, between our single prospective cohort with lower CS vs a historic, retrospective control group (PTx performed during 2011-2013). The incidence of rejection is defined as the fraction of patients in which rejections episodes (one or more) have been proven by biopsies. For SPK rejection in eitherorgan, pancreas or kidney, counts.
- Compare the incidence of *surgical complications*, involving reoperations and reinterventions, between the prospective study group and retrospective control group.

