#### SELECTION OF PATIENTS

- 1. **Inclusion Criteria**Patients will be eligible for study entry if **ALL** of the following criteria are met:
     1. Age ≥18 years
     2. Patients who receive a primary or secondary pancreas transplant, with or without a simultaneous kidney transplant (SPK).
     3. Women who are of childbearing potential must have a negative serum pregnancy test at baseline.
     4. Operability has to be ascertained by preoperativeexamination, performed by nephrologist, transplant surgeon and anesthesiologist.
     5. Signed and dated informed consent form.
  2. Exclusion Criteria

Patients will not be eligible if **ANY** of the following criteria are met:

- - 1. Evidence of systemic infection
    2. Presence of unstable cardiovascular disease.
    3. Malignancy < 5 years prior to entry into the trial (with the exception of adequately treated basal cell or squamous cell carcinomas of the skin).
    4. Panel-reactive antibodies (PRA) > 20% or the presence of donor-specific antigens (DSA).
    5. Any positive test for HBV, HBC or HIV.

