**10. ANALYSIS OF RESULTS**

Even though this is a single cohort observational study (SCOS), we will demonstrate power considerations involving a historic control (HC) group - as if it was a randomized study.

The primary end-points ‘Incidence of rejection’ and ‘Rate of surgical complications’ are both categorical parameters and can be treated similarly in power calculations.

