**10.3 Statistical methods in data analysis**

- The primary evaluation criteria ‘Incidence of rejection’ and ‘Rate of surgical complications’ will be evaluated for several populations:

- All patients who receive at least one dose of study medication, defined as the ‘Intention-to-Treat’ population.

- All patients who complete 12 months of intended study medication, defined as the ‘Intention completed’ population.

The analysis of these categorical parameters will consist of:

1. Comparisons of groups using the Fisher exact test.

2. Confidence intervals of 95% of the percentage of incidence of these

events.

- The loss of grafts and deaths will be analysed by the Kaplan-Meier method for estimating the time to events.
- Continuous (non-categorical) variables will be analyzed by student t-tests and chi-square tests.
- Microdialysis data are typically non-normally distributed. We will therefore use the Wilcoxon Signed rank test for repeated measurements and the Mann-Whitney U test for comparison of groups. We will also use linear mixed model analyses on log10 transformed data for repeated measurements. Receiver operating curves and contingency tables will be used to explore sensitivity and specificity.
- Any other methods that are not planned can be considered as alternative methods.

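### The study cohort is screened on PRA, DSA and other risks, the 2011-2013 control has no stated eligibility rule, and the primary comparison is an unadjusted Fisher test

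*Protocol*

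**What the plan says.** **Study cohort.** The Exclusion Criteria under Selection of patients remove recipients with "Panel-reactive antibodies (PRA) > 20% or the presence of donor-specific antigens (DSA" and those with "Presence of unstable cardiovascular disease". They also remove systemic infection, malignancy within five years, and positive hepatitis or HIV tests. Signed consent is required.

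**Control.** Section 2.1 describes the comparator as a "historic, retrospective control group (PTx performed during 2011-2013" and gives no other condition. No other section applies the selection criteria to it.

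**Analysis.** Section 10.3 sets out, for both primary endpoints, "Comparisons of groups using the Fisher exact test" and 95% confidence intervals. It names no stratification, matching or model for this comparison, and adds only that unplanned methods may be considered as alternatives. Section 10 presents the power considerations "as if it was a randomized study".

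**Prognostic factors the protocol reports.** In section 1.1, when patients with and without reoperation were compared, "higher donor age had a significant negative impact". Female recipients tended to do better. The Introduction says: "Solitary pancreas transplantation (SPT) has traditionally been subjected to even higher complication and rejection rates".

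**Planned covariate work.** Section 2.5 relates donor and recipient characteristics, PRA included, to graft survival and complications. Rejection is not among the outcomes, graft type (SPK or solitary) is not among the characteristics, and the work is not described as adjusting SCOS against HC.

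**The concern.** Without randomisation, the two groups are comparable only if they are selected alike or the analysis corrects for the difference. As written, one group passes an immunological and medical filter, the other passes none that is stated, and the test takes no account of this.

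Rejection is where it matters most. Section 10.1 names failure to detect a raised rejection rate in SCOS as the most important error to avoid. Removing higher-risk patients from SCOS only would push the comparison towards that error. The discontinuation criteria in section 10.4, which look for a doubling relative to HC, rest on the same comparison.

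For surgical complications the filter has no clear direction. Donor age and graft type, which the protocol itself treats as related to outcome, could still differ between the periods and move the crude comparison either way.

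**Working it through.** **1. The protocol's own figures.** Section 10.2 uses N = [Pn(1-Pn) + Ps(1-Ps)] × c / (Pn-Ps)², with an HC rate Pn of 0.30.
- Rejection, 80% power: (0.21 + 0.24) × 7.9 / 0.01 = 355.5 (stated 355).
- Complications, 80% power: (0.21 + 0.16) × 7.9 / 0.01 = 292.3 (stated 292).
- Rejection, 60% power, c = 5.3: 0.45 × 5.3 / 0.09 = 26.5 (stated 27).
- Complications, 60% power, c = 5.3: 0.3375 × 5.3 / 0.0225 = 79.5 (stated 80).

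The figures reproduce. All of them take 0.30 as the rate SCOS would have if the regimens were equal, so they allow for no difference in selection.

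**2. Shift from selection alone.** Let a share f of HC be patients the exclusions would have removed, with r times the rejection risk of the eligible patients. If HC as a whole has a rate of 0.30, the eligible patients have p = 0.30 / (1 - f + f·r). That is the rate expected in SCOS with no treatment effect. The protocol gives neither f nor r, so both are assumed over a range.

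| f | r = 1.5 | r = 2 | r = 2.5 |
|---|---|---|---|
| 5% | 29.3% (0.7) | 28.6% (1.4) | 27.9% (2.1) |
| 10% | 28.6% (1.4) | 27.3% (2.7) | 26.1% (3.9) |
| 20% | 27.3% (2.7) | 25.0% (5.0) | 23.1% (6.9) |
| 30% | 26.1% (3.9) | 23.1% (6.9) | 20.7% (9.3) |

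Cells give the SCOS rate with no effect; brackets give the apparent advantage over HC in percentage points.

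**3. Effect on the planned test.** SCOS is 60-80 (section 5). Section 1.1 gives 22 + 28 = 50 transplants for 2011-2012 and nothing for 2013, so HC = 70 is assumed. The probabilities below come from exact enumeration of the two-sided 5% Fisher test with HC at 0.30, shown for SCOS = 60 / 80.

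| SCOS rate with no effect | SCOS falsely shown better | True one-third increase shown | True doubling shown |
|---|---|---|---|
| 30.0% (no selection) | 2% / 2% | 20% / 22% | 92% / 96% |
| 28.6% | 3% / 3% | 14% / 16% | 86% / 92% |
| 27.3% | 4% / 5% | 10% / 11% | 78% / 86% |
| 25.0% | 8% / 9% | 5% / 5% | 61% / 69% |
| 20.7% | 20% / 23% | 1% / 1% | 25% / 28% |

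**4. The doubling criterion in section 10.4.** For SCOS to be expected at twice the HC rate, the true increase must be 2 × (1 - f + f·r). This is 2.05-fold at f = 5%, r = 1.5; 2.4-fold at f = 20%, r = 2; and 2.9-fold at f = 30%, r = 2.5.

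**The case against.** - **The control's make-up is unknown.** A reader might infer that HC is every 2011-2013 transplant and does retain high-risk patients. Dates without a rule make the first the natural reading, but the protocol does not say it, and it reports no control with PRA above 20%, DSA or any other exclusion. Pre-transplant DSA testing is described as already routine, and section 4 plans to enrol consecutive recipients, which suggests few exclusions were expected. This stands: the missing rule is certain, the bias is not.
- **The shift may be small against what the study can detect.** Section 10.2 calls the numbers behind the 10-point effect unrealistic and falls back on 0.30 against 0.60. Against that 30-point difference, 0.7 to 9.3 points is about 2% to 31%. With 70 per group the standard error of the difference is √(2 × 0.3 × 0.7 / 70), about 7.7 points. This also stands, although the lower rows of the second table show material harm even to detecting a doubling.
- **Both endpoints favouring SCOS is too strong.** The protocol does not link PRA or pre-transplant DSA to surgical complications; its DSA discussion (section 1.3) concerns de novo antibodies and graft outcome.
- **Graft type does not simply mean two organs against one.** Sections 10.1 and 10.4 also count duodenal-segment biopsies, so a solitary graft has more than one tissue in which rejection can be found.
- **The comparison is not offered as a pure steroid effect.** Section 3 calls the study observational, and the rationale in section 2 includes evaluating recent surgical and medical measures. True, but those aims also need groups selected alike.
- **Model detail can sit in an analysis plan.** A plan not shown here may specify adjustment. The definition of the control, however, belongs in the protocol, and section 10.3 already names a crude test.

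**Conclusion.** The point holds as a mismatch in selection between the two groups, left uncorrected by the analysis the protocol names. If HC includes patients the exclusions would have removed, and they carry higher rejection risk, the rejection comparison is biased towards SCOS, and the section 10.4 criterion is affected in the same way. For surgical complications no direction can be given.

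The protocol does not allow the size to be computed. The 0.7 to 9.3 points depend on the assumed 5-30% ineligible share and relative risk of 1.5-2.5, and on 0.30 as the HC rate. The power figures also assume 70 controls. If 2011-2013 practice already declined such patients, the shift could be close to nil, and a chart check would show it. The correction is cheap and should be made before the comparison is run.

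**What to change.** **(a) Section 2.1.** Define HC as 2011-2013 transplants that meet the selection criteria verifiable from charts: age, PRA, pre-transplant DSA, infection, cardiovascular disease, malignancy and viral status. Consent cannot be mirrored and should be left out. Report how many controls are excluded, by criterion, and list those whose charts do not settle the matter. Give the unrestricted HC as a sensitivity analysis, and state which HC the section 10.4 comparison uses.

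**(b) Section 10.3.** Beside the Fisher test, prespecify an adjusted risk difference with very few covariates: SPK versus solitary and donor age, optionally recipient sex. PRA should not be added, because after restriction it has little range left. Record graft type in both groups, since section 2.5 does not list it.

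**Cost.** A chart check of the controls and a somewhat smaller HC. At a 30% rate, 130-150 patients (60-80 plus an assumed 70) give 39-45 events, or 13-15 per term for group plus two covariates. At the roughly 10% solitary share in section 1.1, only 13-15 patients would be solitary, so that coefficient will be imprecise. Neither step removes other differences between the periods, such as the changes in surgical technique and biopsy surveillance described in section 1.1.

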**7 DOSAGE AND ADMINISTRATION**

**7.1 Immunosuppression**
The single cohort study group will receive our routine immunosuppressive regimen based on ATG, tacrolimus, mycophenolate mofetil and corticosteroids as follows:

7.1.1 *ATG (Thymoglobulin):*
Initiated at day 0 (the first dose preop.) at a dose of 2.5 mg/kg i.v.. Later dosing is directed by T-cell counts once daily. The T-cells are kept suppressed for 10 days post-Tx, and new doses of 1.0-2.5 mg/kg i.v. is given whenever the T-cell count rises above 0.050 x109. Altogether, 2-4 doses of ATG are usually needed.

7.2.1.1 *T-cell counts*

Whole blood T-cell counts will be obtained daily from day 1-10.

7.1.2 *Tacrolimus:*

Initiated at day 0 (the first dose preop.) at a dose of 0.06 mg/kg x 2 p.o., later adjusted to achieve steady state whole-blood trough levels as follows:
Month 1-3 8-12 ng/ml
Month 3-6 4-8 ng/ml

7.1.2.1 *Tacrolimus concentration determination*
Whole blood trough concentrations for tacrolimus will be obtained daily from day 1-5, thereafter at least 3 times weekly. Concentrations will also be determined at the time of any serious adverse event.

7.1.3 *Mycophenolate mofetil (MMF):*
MMF will be given 1000 mg twice daily. It can be reduced to 750 mg twice daily in case of adverse events and further down to 500 mg in case of persisting adverse events.

7.1.4 *Corticosteroids:*
Day 0 (perop.): Methylprednisolone 250 mg i.v.

Day 1-14: Prednisolone 20 mg x 1 p.o.

Day 15-28: Prednisolone 15 mg x 1 p.o.

Day 29-60: Prednisolone 10 mg x 1 p.o.

Day 61- 180: Prednisolone 7.5 mg x 1 p.o.

Day 181 - : Prednisolone 5 mg x 1 p.o.

7.2 Concomitant Treatments

7.2.1 Required treatment

i) Prophylaxis against the development of *Pneumocystis carinii*, with trimethoprim-sulfa is required for all patients during the first 6 months

of treatment.
 ii) Prophylaxis against Cytomegalovirus (CMV) with valganciclovir for 3 months, if the donor is CMV + and the recipient is CMV ÷.

By all other CMV constellations, *preemptive* valganciclovir treatment is given, based on weekly CMV-PCR analyses (cut off: CMV-PCR count > 0).

iii) Antibiotic prophylaxis with meropenem (2 doses) and vancomycin (1 dose) at day 0.

iv) Proton pump inhibitor (pantoprazol/esomeprazole) is given for at least 2 months post-Tx.

7.2.2 Prohibited treatment

i) Investigational study drugs

ii) NSAID’s should be avoided

iii) Terfenadine, cisapride, astemizole, pimozide, cimetidine and

ketoconazole are not allowed.

**8 TREATMENT OF ACUTE REJECTION EPISODES**

P-, tD and K-biopsies must be examined in all suspected cases of rejection. This investigation should be performed before anti-rejection therapy is commenced, or at least within 24 hours of start of treatment. Whenever possible, anti-rejection therapy should be postponed until a histological diagnosis of rejection is confirmed. Acute rejection should be treated with boluses of methylprednisolone first-line according to our local practice for both pancreas- and Kidney-Tx. For *steroid resistant rejections* (defined as: no pancreas/kidney functional improvement after at least 4 boluses of methylprednisolone or rejection in repeat D-, P- or K-biopsies), ATG therapy should be initiated and administered for 7-14 days. Some cases of severe rejection may be treated with ATG primarily – also to reduce the prodiabetic steroid load.

Hyperglycemia caused by steroid dosing will be treated by subcutaneous injections of insulin, alternatively iv insulin infusion, according to current guidelines at the hospital.

All biopsies will be examined at our local pathology unit; the pancreas and duodenal biopsies by prof. [name] and dr. [name]; the kidney biopsies by prof. [name] and dr. [name].

**9 ADVERSE EVENTS**

All adverse events will be recorded in the appropriate section of the case record form (CRF), regardless of whether or not they are assumed to be related to the applied treatment. The nature of adverse event, details or severity, together with the date of onset, duration and outcome will be recorded. The investigator’s opinion on the relationship of the adverse event to the treatment will also be recorded.

**9.1 Definitions**
An adverse event is any adverse change from the patients baseline (pre-Tx) condition, including intercurrent disease(s) occurring during the course of the study after the treatment has started, whether considered related to treatment or not. Treatment includes all agents administered during the course of the study.

Clinical adverse events must be graded on a three-point scale (mild, moderate and severe) and be reported in the appropriate sections of the case record form.

**Mild:** Awareness of symptoms but easily tolerated

**Moderate:** Discomfort enough to interfere with normal activities

**Severe:** Completely prevents normal activities

The relationship between the adverse event and the treatment must also be assessed as follows:

**Definite:** The experience meets the following criteria:

- followed a reasonable temporal sequence from drug administration
- compatible with known drug profile
- abated upon discontinuation of the drug (dechallenge)
- with or without documentation that the experience was confirmed by reappearance of the reaction on repeat exposure (rechallenge)

**Probable:** The experience meets one or more of the following criteria:

- follows a reasonable temporal sequence from drug administration
- compatible with known drug profile and cannot be reasonably explained by the known characteristics of the patient’s clinical state
- with or without documentation that the experience abates upon

discontinuation of the drug (dechallenge)

**Possible:** The experience meets the following criteria:

- follows a reasonable temporal sequence from drug administration
- could have been produced by the patient’s clinical state or by the drug in question
- compatible with known drug profile

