**9.3 Serious Unexpected Adverse Drug Reaction (ADR)**

A Serious Unexpected adverse drug reaction is defined as reaction which in the opinion of the Investigator is thought to be definitely, probably or possibly drug related and has not previously been known to occur for that drug either from the literature, adverse event listings or Investigator experience - but is not a common clinically insignificant illness.

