**9.4 Follow Up of Adverse Events**

Any abnormal laboratory values, abnormal clinical findings and adverse events which are of clinical significance, in the opinion of the investigator, must be followed with appropriate medical management until resolved.

Individual patients will be excluded from the study if serious adverse effects related to the treatment is observed.

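### Section 9.1 sets the boundary between Probable and Possible the wrong way round: plausible timing alone earns Probable, while Possible needs timing plus two further criteria

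*Protocol*

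**What the plan says.** Section 9.1 of the protocol makes the causality grading mandatory and lists six grades. Three of them describe related events:

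- **Definite** applies when "The experience meets the following criteria": temporal sequence, compatible drug profile and abatement on dechallenge. A last line says with or without confirmation by rechallenge.
- **Probable** applies when "The experience meets one or more of the following criteria". The first criterion listed is "follows a reasonable temporal sequence from drug administration". The second asks for a drug profile that fits and for an event that the clinical state does not reasonably account for. The third begins "with or without documentation that the experience abates upon" and goes on to name dechallenge.
- **Possible** applies, as Definite does, when "The experience meets the following criteria": the same temporal sequence, a compatible profile, and that the event "could have been produced by the patient’s clinical state or by the drug in question".

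Remote, Definitely Not and Unknown follow. No sentence says which grade prevails when an event fits more than one.

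Relatedness is used twice afterwards. Section 9.3 defines a serious unexpected reaction as one "thought to be definitely, probably or possibly drug related" in the investigator's opinion and not previously known for that drug. Section 9.4 states: "Individual patients will be excluded from the study if serious adverse effects related to the treatment is observed".

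**The concern.** A causality scale works only if a higher grade takes more evidence than a lower one. Here the middle grade is the easiest to reach, because it alone uses an any-one rule.

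The criterion that suffices for it, timing, separates events poorly in this study. The flow chart in section 15 shows tacrolimus, mycophenolate and corticosteroids given continuously from day 0, and section 9.1 defines treatment as all agents administered during the study. Many post-transplant events will follow some drug in a reasonable time sequence.

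What is at stake is the meaning of the recorded grades, and which serious events pass the relatedness part of 9.3. Two assessors could also give the same event different grades, both within the text.

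**Working it through.** The protocol gives no figure to reproduce, so the check is one of logic.

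**Rules as written.** Let T = reasonable temporal sequence, C = compatible drug profile, X = not reasonably explained by the clinical state, A = abates on dechallenge, R = reappears on rechallenge, B = could be due to clinical state or drug.

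- Definite = T and C and A (the rechallenge line adds no requirement)
- Probable = T, or (C and X), or the with-or-without dechallenge line if that line is read as a criterion
- Possible = T and B and C

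**Direct consequences.** Possible contains T, and T alone gives Probable, so Possible implies Probable. With T true and C false, Possible fails and Probable holds. Neither step uses the dechallenge line.

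**Enumeration.** Six yes/no attributes give 64 profiles. X and B contradict each other, so the 16 profiles with both are removed: 64 − 16 = 48.

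- Probable, dechallenge line treated as a note: T true gives 24; T false with C and X true and B false gives 4 (A and R free). Total 28.
- Probable, dechallenge line treated as a criterion: 48, since the line is true of every event. The extra 48 − 28 = 20 qualify through that line alone.
- Possible: T, B, C true, X false, A and R free: 4.
- Definite: T, C, A true, three admissible X/B pairs, R free: 3 × 2 = 6. All have T, so all meet Probable.
- Probable on timing without a compatible profile: T true, C false, three X/B pairs, A and R free: 3 × 4 = 12. None of these meets Definite or Possible.

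| Reading | Probable | Possible | Possible is the highest grade met | Definite |
|---|---|---|---|---|
| As written, dechallenge line a criterion | 48 | 4 | 0 | 6 |
| As written, dechallenge line a note | 28 | 4 | 0 | 6 |
| All Probable criteria required | 4 | 4 | 2 | 6 |
| The same, with X added to Definite | 4 | 4 | 4 | 2 |

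In the third row, 2 of the 4 Possible profiles also meet Definite while failing Probable, so changing Probable alone leaves the scale disordered. In the fourth row Definite needs T, C, X and A with R free, which is 2 profiles, both inside Probable, and Possible stands separately.

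These are counts of logical profiles, not expected event frequencies.

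**Link to 9.3.** Definite, Probable and Possible all count there, so confusing the last two changes nothing by itself. What changes is that events with timing only, which fail both Definite and Possible, enter through Probable. Conversely, a truly new reaction may not match the known drug profile. As written, the loose Probable rule is its only way into a related grade. Tightening Probable without touching 9.3 could close that route.

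**The case against.** The strongest reply is that little depends on the scale. Section 9 records the investigator's opinion, and a sensible investigator will grade a surgical bleed as Remote or Definitely Not, the latter expressly covering events produced by other therapy. All adverse events are recorded whatever their relatedness. The primary endpoints (2.1, 10.1) and the discontinuation criteria (10.4) count events without a causality grade, and 10.3 plans no analysis by relatedness. Section 9.4 names no grade of the scale. All of this stands, and it limits the importance of the point. It does not remove it: 9.1 lays the definitions down as the way to assess, and an investigator who reaches sensible grades by setting them aside is not applying them.

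Three stronger readings are tempting and not supported.

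- *Every event is Probable.* This follows only if the with-or-without line is read as a criterion in its own right. The same form closes the Definite list, where it can only be a note. Read consistently, it is a note under Probable too.
- *The whole scale is inverted.* Only Probable and Possible are out of order. Every event that meets Definite as written also meets Probable, and Definite still requires dechallenge.
- *Some 18 to 24 patients will be misgraded.* A reader could multiply the reoperation rate of about 30% in section 1.1 by 60 to 80 patients (0.30 × 60 = 18; 0.30 × 80 = 24). That counts patients reoperated if the 2006–2010 rate persists. It says nothing about how their events would be graded, and Remote and Definitely Not remain open for them.

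**Conclusion.** The point holds as a minor error of definition. The Probable and Possible rules in 9.1 are out of order: no event can be Possible without also being Probable, and timing without a compatible drug profile gives Probable. This rests on reading the Possible criteria as jointly required, which their introductory line, set against the different one under Probable, supports.

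The reach is the recorded relatedness grades, the 9.3 classification (where an event must still be serious and previously unknown) and possibly the 9.4 exclusion, depending on which grades that section means by related. The number of events affected cannot be estimated from the protocol. The primary comparisons and the stopping criteria are untouched.

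**What to change.** In section 9.1:

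1. Under Probable, replace the any-one rule by a requirement that all criteria are met.
2. Under Probable and Definite, take the with-or-without lines out of the criteria and set them as notes.
3. Add to Definite the requirement, already in the second Probable criterion, that the clinical state does not reasonably explain the event. Definite then sits inside Probable.
4. State that an event takes the highest grade whose criteria are all met, and that Remote or Definitely Not applies only when no higher grade is met.

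Reword 9.1 and 9.3 together, so that the compatible-profile criterion does not exclude from the related grades a reaction that 9.3 requires to be previously unknown.

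The cost is a few sentences in 9.1 and 9.3, a matching change to the CRF adverse-event page, and possible regrading of events already recorded. The edit changes no dose or treatment.
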